## Abstract

**Background:**

Bubonic plague is the primary manifestation of infection with *Yersinia pestis*, accounting for 90% of all plague cases and with 75% of global cases reported in Madagascar. All drugs in use for treating plague are registered based on experimental data and anecdotal evidence, and no regimen currently recommended is supported by a randomized clinical trial. The IMASOY trial intends to fill this knowledge gap by comparing two 10-day regimens included in the national guidelines in Madagascar. The primary objective of the trial is to test the hypothesis that ciprofloxacin monotherapy is non-inferior to streptomycin followed by ciprofloxacin for the treatment of bubonic plague, thus avoiding the need for injectable, potentially toxic, aminoglycosides.

**Methods:**

A two-arm parallel-group randomized control trial will be conducted across peripheral health centres in Madagascar in five districts. Males and non-pregnant females of all ages with suspected bubonic or pneumonic plague will be recruited over the course of three plague ‘seasons’. The primary endpoint of the trial is to assess the proportion of patients with bubonic plague who have a therapeutic response to treatment (defined as alive, resolution of fever, 25% reduction in the size of measurable buboes, has not received an alternative treatment and no clinical decision to continue antibiotics) as assessed on day 11.

**Discussion:**

If successful, the trial has the potential to inform the standard of care guidelines not just in Madagascar but in other countries afflicted by plague. The trial is currently ongoing and expected to complete recruitment in 2022.

**Trial registration:**

ClinicalTrials.gov NCT04110340. Registered on 1 October 2019

Role of sponsor {5c}	In collaboration, the University of Oxford, Institut Pasteur de Madagascar (IPM), University Hospital Joseph Raseta Befelatanana Antananarivo, Centre Infectiologie Charles Mérieux Madagascar are responsible for the design and management of the IMASOY trial. The University of Oxford and IPM are jointly responsible for data collection and management. All collaborators will be responsible for writing and publishing the final report. The London School of Hygiene and Tropical Medicine is primarily responsible for the statistical analysis, alongside IPM de Madagascar and the University of Oxford. Any further publications that arise following the dissemination of the final report will be reviewed by the University of Oxford before their release. All publications will be open-access. Laboratory data analysis will be the responsibility of IPM.

## Introduction

### Background and rationale {6a}

#### Plague

Plague is caused by the Gram-negative bacteria *Yersinia pestis*. There are three main clinical forms in which plague can manifest, sometimes with overlapping clinical syndromes: bubonic plague, septicaemic plague (primary or secondary) and pneumonic plague (primary or secondary) [1]. Bubonic plague is the most common clinical form and is characterized by the rapid onset of fever and tender and painful lymphadenopathy. It accounts for over 90% of plague cases [1]. Septicaemic plague is characterized by non-specific symptoms, as for septicaemia in general [1]. Pneumonic plague presents with rapid onset of fever and respiratory symptoms, with haemoptysis being a cardinal feature [1].

Plague is primarily present in Africa, although the USA and countries in Asia and South America are also affected. The incidence of plague continues to decrease (from 2683 cases notified to the WHO in 2008 to 243 in 2018) and geographical spread to shrink (98% of reported cases currently from just Madagascar and the Democratic Republic of Congo (DRC)) [2]. However, the reservoir and conditions for transmission are still present in many areas of the world, and there is a risk of outbreaks when plague hits densely populated areas, as in the 2017 large urban outbreak of predominantly pneumonic plague in Madagascar, with over 2400 suspected cases [3].

In the pre-antibiotic era, the case fatality rate (CFR) of plague was > 70% [4]. Antibiotics have significantly reduced mortality: for the cases notified to WHO during 2010–2018 CFR averaged 17% [2]. During the 2017–2018 plague outbreak in Madagascar, the CFR of confirmed pneumonic plague was 25% and bubonic plague 24% [3].

#### Current treatment options

Until July 2018, the 1st-line treatment regimen for bubonic plague in Madagascar was streptomycin (days 1 to 5) followed by cotrimoxazole (days 3 to 8). Following the 2017 epidemic, an After Action Review was conducted and treatment guidelines for bubonic plague were modified to include, for adults, either streptomycin intramuscularly 1 g (except pregnant women) or gentamicin 2.5 mg/kg twice daily for 3 days, followed by ciprofloxacin 500 mg twice daily for an additional 7 days or ciprofloxacin alone at 500 mg twice daily for 10 days. Intravenous ciprofloxacin at a dose of 400 mg every 12 h can be used if the oral route is not possible. Treatment options in children are now either oral ciprofloxacin 15 mg/kg twice daily for 10 days or, if oral administration is not initially possible, streptomycin 15 mg/kg every 12 h intramuscularly for 3 days followed by ciprofloxacin 15 mg/kg twice daily for an additional 7 days.

The first-line treatment regimen for pneumonic plague in adults is streptomycin 1 g intramuscularly twice daily for 5 days combined with ciprofloxacin 500 mg orally twice daily for 10 days, and for children, intravenous gentamicin at 2.5 mg/kg every 12 h for 5 days (or streptomycin) combined with oral ciprofloxacin at 15 mg/kg every 12 h for 10 days (with the possibility of intravenous ciprofloxacin at 15 mg/kg every 12 h if the oral route is not available). The maximum dose for ciprofloxacin is 500 mg per oral dose and 400 mg per intravenous dose for children.

Streptomycin alone or in other combination therapies is also the treatment of choice in other countries, including the DRC and Peru.

#### Study rationale

The evidence base for the current treatment regimens for plague is weak, and none is supported by a randomized clinical trial (RCT). Two randomized control trials have previously attempted to improve on or contribute to a better evidence base for current plague treatment regimens [5, 6]. However, neither trial was successful nor included children under 8 years of age, who constitute a significant proportion of the population affected by plague. Treatment recommendations are based on animal models, case reports, case series and a trial of doxycycline versus gentamicin [5]. All drugs approved for treating plague by the the United States Food and Drug Administration (US FDA) (streptomycin, tetracyclines and the fluoroquinolones ciprofloxacin, levofloxacin and moxifloxacin) are registered based on the ‘animal efficacy rule’, in the absence of clinical data [7]. Political instability and practical difficulties related to highly dispersed cases in rural areas have been the major obstacles to conducting treatment trials of plague.

The main issue with current regimens in Madagascar is the use of aminoglycosides—with the need for injections, class toxicity and need for monitoring of renal and auditory functions, which is not routinely available in most low- and middle-income countries, and streptomycin cost and stock-outs.

Ciprofloxacin is cheaper, more readily available in low- and middle-income countries, has greater ease of administration and there is no need for biochemical or drug monitoring. There is also no reason to believe that there is a difference in effectiveness. These reasons would likely result in ciprofloxacin being the first-line choice for the treatment of plague should it be shown to be effective.

### Objectives {7}

The primary objective of this trial is to test the hypothesis that ciprofloxacin monotherapy given (orally, or for subjects who cannot take oral medications intravenously or in combination) for 10 days is non-inferior to streptomycin (given on days 1–3) followed by ciprofloxacin (given on days 4–10) for the treatment of bubonic plague. The regimens are respectively third- and first-line treatments as per the national plague treatment guidelines in Madagascar.

The secondary objective is to collect data on the effectiveness of ciprofloxacin in the treatment of pneumonic plague, although the trial is not able to formally assess the non-inferiority of ciprofloxacin monotherapy compared to streptomycin and ciprofloxacin combination therapy in pneumonic plague,

Considering the operational and practical complexities of a plague RCT, the study also has additional exploratory objectives to optimize investments: to evaluate the level and kinetics of anti-*Y. pestis* antibodies in bubonic and pneumonic plague during treatment and follow-up, to compare different methods for detection of anti-*Y. pestis* antibodies, to measure the performance of qPCR for plague diagnosis and to allow for the evaluation of new rapid tests that may become available.

### Trial design {8}

#### Study schematics

This is an individually randomized two-group parallel arm control trial with a 1:1 ratio. Patients will be randomized to receive either streptomycin + ciprofloxacin or ciprofloxacin alone. We are using a non-inferiority design since the overall cure rate for bubonic plague without septicaemia with streptomycin is expected to be 90%. As a result, demonstrating superiority would be unnecessary and impractical given the sample size that would be required. Our aim is therefore to demonstrate that ciprofloxacin alone is not more than 15% inferior to streptomycin followed by ciprofloxacin (15% is the non-inferiority margin in our study, meaning that the lower bound of the confidence interval around the risk difference in the success rates of streptomycin + ciprofloxacin and ciprofloxacin alone must not include 15%). The trial is powered for bubonic plague, although we will recruit patients with pneumonic plague as well.

#### Box 1—Case definitions

**Table Tabb:** 

Probable and confirmed cases are defined as:	
Probable case: rapid diagnostic test (RDT) or qPCR or serology (anti-F1 IgG ELISA) is positive but without evidence of seroconversion or a fourfold increase in antibody titre.	
Confirmed case: RDT and qPCR are positive, or culture is positive, or there has been a seroconversion or a fourfold increase in antibody titre on two separate serological samples (either between D1 and D11, between D11 and D21 or between D1 and D21).	

We will recruit patients with clinical suspicion of bubonic plague, but the size of our sample is powered based on an intention to treat infected patient sample size of 190, where ‘infected’ is defined as a ‘confirmed’ or ‘probable’ case of bubonic plague. As a result, the total number of patients to be enrolled will be higher than 190. We estimate that we will need to recruit approximately 600 patients with bubonic plague to achieve a sample size of 190 confirmed/probable bubonic plague patients. However, to mitigate risks of being under-powered, we will recruit for three full seasons (2019–2022) with a minimum target of 190 confirmed/probable cases, 95 patients in each arm.

Should we achieve the target of 190 confirmed/probable bubonic plague cases before the end of the third season (2019–2022), we will nevertheless continue to recruit until the end of the season to retain power in the event the observed treatment success rates differ from those expected, and to allow us to increase precision.

Whilst we will also recruit and collect data on patients with pneumonic plague, it is highly unlikely that we will have the power to complete a non-inferiority trial for ciprofloxacin monotherapy for pneumonic plague patients. For example, with a case fatality rate of 20–25%, we would need a sample size of approximately 400 patients with probable/confirmed pneumonic plague for a non-inferiority margin of 15%, which is unrealistic.

#### Study timelines

Recruitment is expected to last 3 years and will take place during each ‘plague season’ (the annual high transmission period of plague, which starts at the beginning of August and runs until the following March).

#### Study population

The study will enrol males and non-pregnant females of any age with suspected bubonic or pneumonic plague.

## Methods: participants, interventions and outcomes

### Study setting {9}

#### Study setting

The trial will take place in up to five pre-identified districts in Madagascar. Madagascar reports more plague cases per year than any other country with an average number of confirmed/probable cases per year of 387 [8].

#### Study sites

Recruitment is planned to take place in 50 health centres (primary health centres (Centres de Santé de Base, CSB) and district hospitals) in five districts. Recruiting districts and sites have been selected based on their incidence of plague (as reported to IPM) and also for logistical reasons. However, the trial may be carried out in further districts or sites depending on the real-time incidence of suspected cases of plague during the study period. The majority of plague patients are treated at the CSB level. In general, CSBs do not have a laboratory, so sites perform an RDT to obtain a preliminary diagnosis and then send further samples to IPM for confirmation where a second RDT, qPCR and culture are routinely performed.

### Eligibility criteria {10}

#### Inclusion criteria

##### Bubonic plague

Patients of any ageRecent onset (< 10 days) of fever (uncorrected axillary temperature ≥ 37.5 °C) or history of feverOne or more buboes (tender lymph node swelling)Residence or travel to a plague endemic or outbreak area in Madagascar within 14 days of the onset of symptomsPatients identified as clinically suspected of plague by health personnel (doctors or paramedics)

##### Pneumonic plague

Patients of any ageRecent onset (< 7 days) of fever (uncorrected axillary temperature ≥ 37.5 °C) or history of feverCoughTachypnoea (respiratory rate > 24 in adults and age-specific in children)Epidemiological link with a confirmed or probable case of primary or secondary pneumonic plague within 7 days of onset of symptoms

A small proportion of patients with bubonic plague will also develop pneumonic plague. These patients will be randomized to receive pneumonic plague therapy. For a patient to be considered to have mixed bubonic and pneumonic plague, they must have developed cough and dyspnoea after the onset of the bubo.

#### Exclusion criteria

Known allergy to aminoglycosides or fluoroquinolonesTendinitisMyasthenia gravisTheophylline or warfarin useAlready treated for bubonic or pneumonic plague in the preceding 3 monthsWomen who report being pregnant

Given that streptomycin is an FDA class D drug, women who report being pregnant will not be randomized into the trial but will be treated outside the trial according to the national guidelines. Lactating women can safely be treated with streptomycin as streptomycin poses minimal risk to the infant when used during breastfeeding and will therefore be randomized into the trial.

### Who will take informed consent? {26a}

All eligible patients will be offered the opportunity to participate in the study. Patient information sheets, consent and assent forms will be available in relevant written local languages. Written informed consent to participate will be required from all participants or their representatives and will be requested by local study staff, who are qualified, trained and authorized to do so by the principal investigator.

### Additional consent provisions for collection and use of participant data and biological specimens {26b}

Patients are fully informed about the use of biological specimens and their data in the patient information sheet, including lay descriptions of the procedures for collecting samples and details about data and sample storage.

## Interventions

### Explanation for the choice of comparators {6b}

Both treatment regimens tested are provided for by the national guidelines. There are several reasons why streptomycin is a suboptimal therapeutic agent for plague including global stock shortages, the requirement for parenteral administration and severe toxicity.

In vitro assays suggest that ciprofloxacin has comparable efficacy to streptomycin and is superior to doxycycline or gentamicin for the killing of intracellular *Y. pestis* [6]. Studies in non-human primates of pneumonic and bubonic plague have also shown high therapeutic efficacy of ciprofloxacin, equivalent to streptomycin [9, 10]. Ciprofloxacin also offers the advantage of the possibility of a switch from intravenous to oral treatment if clinically appropriate, does not require drug level or renal function monitoring, has fewer and less severe side effects, it is classed by the US FDA as pregnancy category C (whereas other treatment alternatives are category D), has greater global availability and is cheaper. Unlike other treatment alternatives, ciprofloxacin can be administered to children.

### Intervention description {11a}

#### Dosing schedule in bubonic plague

##### Ciprofloxacin arm

Adults: 500 mg orally twice daily (or 400 mg IV twice daily for those who cannot take oral medication) for 10 days.Children: 15 mg/kg twice daily (max 500 mg per dose) orally (or 10 mg/kg IV twice daily for those who cannot take oral—maximum dose 400 mg) for 10 days.Patients who begin intravenous therapy may switch to oral administration once they are able to swallow or once deemed clinically appropriate by the treating physician.

##### Control arm

Adults: streptomycin 1 g twice daily for 3 days, followed by ciprofloxacin 500 mg orally twice daily (or ciprofloxacin 400 mg twice daily by IV for those who cannot take it orally) for an additional 7 days.Children: streptomycin 15 mg/kg twice daily for three days followed by ciprofloxacin 15 mg/kg twice daily (max 500 mg per dose) orally (or 10 mg/kg IV twice daily for those who cannot take oral—maximum dose 400 mg) for 7 additional days.Patients who start taking intravenous ciprofloxacin may switch to oral administration once they are able to swallow or once deemed clinically appropriate by the treating physician.

#### Dosing schedule in pneumonic plague

##### Ciprofloxacin arm

Adults: 500 mg orally twice daily (or 400 mg IV twice daily for those who cannot take oral medication) for 10 days.Children: 15 mg/kg twice daily (max 500 mg per dose) orally (or 10 mg/kg IV twice daily for those who cannot take oral—maximum dose 400 mg) for 10 days.Patients who begin intravenous therapy may switch to oral administration once they are able to swallow or once deemed clinically appropriate by the treating physician.

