##### Control arm

Adults: streptomycin 1 g twice daily for 5 days with ciprofloxacin 500 mg orally twice daily (or ciprofloxacin 400 mg twice daily IV for those who cannot take it orally) for 10 days.Children: streptomycin 15 mg/kg twice daily for 5 days with ciprofloxacin 15 mg/kg twice daily (max 500 mg per dose) orally (or 10 mg/kg IV twice daily for those who cannot take it orally—maximum dose 400 mg) for 10 days. This is the alternative treatment proposed by the Ministry of Public Health since the 2018–2019 plague season.Patients who start taking intravenous ciprofloxacin may switch to oral administration once they are able to swallow or once deemed clinically appropriate by the treating physician.

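### For children with pneumonic plague, the intravenous ciprofloxacin dose in both trial arms differs, without explanation, from the national guideline dose that the protocol itself quotes

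*Protocol article*

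**What the plan says.** Four places in the protocol article bear on this point.

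- **Current treatment options (background).** The paragraph on pneumonic plague describes first-line treatment in children as an aminoglycoside combined with oral ciprofloxacin, "with the possibility of intravenous ciprofloxacin at 15 mg/kg every 12 h if the oral route is not available". It adds: "The maximum dose for ciprofloxacin is 500 mg per oral dose and 400 mg per intravenous dose for children". The paragraph on bubonic plague gives children either oral ciprofloxacin or, "if oral administration is not initially possible, streptomycin 15 mg/kg every 12 h intramuscularly for 3 days followed by ciprofloxacin 15 mg/kg twice daily". It states no intravenous ciprofloxacin dose for children.
- **Dosing schedule in pneumonic plague {11a}.** The ciprofloxacin arm gives children who cannot take oral drugs "10 mg/kg IV twice daily for those who cannot take oral—maximum dose 400 mg". The control arm gives "10 mg/kg IV twice daily for those who cannot take it orally—maximum dose 400 mg", alongside streptomycin, and says of the paediatric regimen: "This is the alternative treatment proposed by the Ministry of Public Health since the 2018–2019 plague season".
- **Dosing schedule in bubonic plague {11a}.** Both arms carry the same intravenous option for children: 10 mg/kg twice daily, maximum 400 mg.
- **Explanation for the choice of comparators {6b}.** "Both treatment regimens tested are provided for by the national guidelines". The sentence names no clinical form of plague.

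**The concern.** In pneumonic plague, the background and the schedules agree on the drug, route, age group, frequency and 400 mg cap. The paediatric oral dose agrees as well (15 mg/kg, maximum 500 mg). Only the intravenous mg/kg figure differs, and no section says why. A reader cannot tell whether the trial departs from the guideline on purpose, whether the background misquotes the guideline, or whether the schedules contain an error.

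Two things are at stake. The first is safety-relevant. Under Route of administration, the intravenous route is for patients who are vomiting, unable to swallow, unconscious or hypotensive, or for whom the physician judges it necessary. An unexplained discrepancy in the dose for such children should not stand. The second is the description of the trial. Section {6b} presents the tested regimens as guideline regimens, and the control-arm text attributes the paediatric pneumonic regimen to the Ministry. The article's own account of the guideline does not bear this out for the intravenous dose.

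**Working it through.** **Inputs**

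- Guideline as quoted, children with pneumonic plague: 15 mg/kg every 12 h, cap 400 mg (Current treatment options).
- Trial schedule, children with pneumonic plague, both arms: 10 mg/kg twice daily, cap 400 mg ({11a}).

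The frequency is the same, so doses can be compared one to one.

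**Step 1: difference per kilogram.** (15 − 10)/15 = 33.3%.

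**Step 2: weight at which each dose reaches the cap.** 400/15 = 26.7 kg for the quoted guideline dose; 400/10 = 40 kg for the trial dose.

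**Step 3: difference by body weight w.** Difference = 1 − min(10w, 400)/min(15w, 400). Between 26.7 and 40 kg this reduces to 1 − w/40.

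| Weight (kg) | Trial schedule (mg) | Guideline as quoted (mg) | Difference |
|---|---|---|---|
| 10 | 100 | 150 | 33.3% |
| 20 | 200 | 300 | 33.3% |
| 26.7 | 267 | 400 | 33.3% |
| 30 | 300 | 400 | 25% |
| 35 | 350 | 400 | 12.5% |
| 40 and above | 400 | 400 | 0% |

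The percentages take the quoted guideline figure as denominator for convenience only; this does not imply that it is the correct one.

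**Step 4: bubonic plague.** The same calculation cannot be made. The background quotes no intravenous ciprofloxacin dose for children with bubonic plague, so there is nothing to set against the 10 mg/kg in those two arms. All that can be said is that the schedules contain an option that the guideline, as quoted, does not mention.

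**Step 5: comparison between arms and sample size.** Within each clinical form, both arms state the same intravenous mg/kg dose, so the difference between the arms in that figure is zero. The sample size does not use it either. With 90% response in both groups, a 15-point margin, one-sided 2.5% and 90% power, n per arm = (1.960 + 1.282)² × 2 × 0.90 × 0.10/0.15² ≈ 84.1, rounded up to 85. Then 85/0.90 = 94.4, rounded up to 95 per arm, or 190 in total, as stated.

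**The case against.** The strongest reply is that the four operative schedules agree with one another and the background is not a dosing instruction. Sites are trained on the protocol and retrained each season, with study nurses working alongside them. This stands. A reader might infer that sites will give different doses depending on which section they follow, but nothing in the article supports that.

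A second reply is that {6b} may refer only to the bubonic regimens. The Objectives section ranks the bubonic regimens within the national guidelines, and the background quotes no ciprofloxacin monotherapy for pneumonic plague at all. The control-arm text also calls its regimen an alternative, whereas the background describes first-line treatment. This has force: no section states outright that 10 mg/kg is the guideline dose. But {6b} carries no such limit, and the word alternative does not account for the dose, since the background already names streptomycin as an option for these children.

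Three stronger readings are tempting and are not supported:

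- **That every trial arm is one third below the guideline.** The 15 mg/kg intravenous figure is quoted for pneumonic plague only.
- **That the discrepancy works against the ciprofloxacin arm**, because control patients also receive streptomycin in the first days. The arms do differ in how far they rely on ciprofloxacin early on, but that is the design under test. The stated intravenous dose is the same in both. In pneumonic plague, control children receive ciprofloxacin for all 10 days, and that form is not formally tested for non-inferiority.
- **That the trial dose is too low.** The background could equally be the section in error.

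**Conclusion.** The contradiction is real and confined to children with pneumonic plague who weigh less than 40 kg and need intravenous ciprofloxacin. For them the article's two figures differ by one third up to 26.7 kg, and by a share that falls to zero between there and 40 kg. For bubonic plague there is a lesser gap: the paediatric intravenous option has no counterpart in the guideline as quoted.

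This rests on the article's own account of the guideline, which cannot be checked here. How many children start on the intravenous route, and at what weights, is not stated, so the number affected is unknown. The point leaves the sample size and the primary non-inferiority comparison as they are. It should still be corrected, because it concerns a dose given to severely ill children and the statement of what the trial tests. Which figure is right cannot be decided from the document.

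**What to change.** Check the paediatric intravenous ciprofloxacin figure in Current treatment options and in the two pneumonic schedules of {11a} against the national guideline, and reconcile them so that they agree. Check the paediatric intravenous option in the two bubonic schedules in the same way. If the trial departs from the guideline on purpose, say so in {11a} with the reason, and qualify the statement in {6b}, naming the clinical form and route to which it applies. No dose is proposed here; that is for the sponsor and the clinical investigators.

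The cost is a textual clarification, with a note to sites if an operative schedule changes. No extra patients, procedures or analyses are needed.
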